# A double-blind, randomized, crossover trial protocol of whole hemp seed protein and hemp seed protein hydrolysate consumption for hypertension

**DOI:** 10.1186/s13063-020-4164-z

**Published:** 2020-04-23

**Keywords:** Casein, Hemp seed protein, Bioactive peptides, Hypertension

## Abstract

**Background:**

Primary hypertension accounts for almost 95% of all cases of high blood pressure and is a major modifiable risk factor for cardiovascular diseases. Lifestyle interventions have been shown to prevent hypertension. One of the prominent potential therapeutic lifestyle strategies to prevent or manage hypertension is increasing dietary protein as a macronutrient or as bioactive peptides. An emerging plant-based protein source that may have anti-hypertensive properties is hemp seed.

**Methods/design:**

A randomized, double-blind, crossover clinical trial will be conducted on 35 hypertensive participants aged 18–75 years, with a BMI between 18.5 and 40 kg/m^2^, systolic blood pressure (SBP) between 130 and 160 mmHg and diastolic blood pressure (DBP) ≤ 110 mmHg. The trial will be conducted for a period of 22 weeks and will consist of three treatment periods of 6 weeks, separated by 2-week washout periods. The treatments will be consumed twice a day and consist of 25 g casein, hemp seed protein (HSP), or HSP plus HSP hydrolysate (HSP+). The primary outcome of this trial is 24-h SBP, measured on the first day of first phase and the last day of each phase. Office-measured blood pressure, pulse-wave velocity and augmentation index and anthropometrics will be determined at the first and last days of each period. Also, body composition will be assessed by dual x-ray absorptiometry (DXA) scan on the first day of the first phase and within the last 2 days of each treatment period. Blood samples will be collected on the first and last 2 days of each treatment phase whereas urine samples will be collected on the first day of the first phase plus the last day of each phase to be analyzed for specific biomarkers.

**Discussion:**

This trial protocol is designed to evaluate the hypotensive potential of consuming whole HSP, and HSP+, in comparison to casein protein. This study will be the first trial investigating the potential anti-hypertensive benefit of dietary hemp protein plus bioactive peptide consumption in humans.

**Trial registration:**

National Clinical Trial (NCT), ID: NCT03508895. Registered on 28 June 2018. Retrospectively registered on the publicly accessible Registry Databank at ClinicalTrials.gov (http://ClinicalTrials.gov).

## Background

Hypertension afflicts over 7.3 million Canadians [1] and is the number-one modifiable risk factor for death and disability globally [2], accounting for 13.5% of all global premature deaths [3]. Over the last 25 years, treatments to control hypertension have increased markedly in Canada [4]; however, one third of the diagnosed hypertensive population remains uncontrolled and many people remain undiagnosed. Uncontrolled hypertension can lead to a spectrum of diseases including stroke, coronary artery disease, as well as heart and kidney failure [5].

The exact etiology of the development and progression of primary hypertension remains uncertain; however, both genetic and lifestyle factors, including diet in particular, have been implicated. Many interconnected contributing factors have been proposed to explain the increase in blood pressure (BP) leading to hypertension. Factors include over-activation of the renin-angiotensin-aldosterone system (RAAS), endothelial dysfunction, elevated sympathetic activation, and other genetic predispositions [6–8]. Current therapeutic agents for BP control have proven to be reasonably effective; however, the incidence of mortality due to high BP is still on the rise [9]. Consequently, an important need exists for alternative therapeutic strategies to prevent or manage hypertension.

Lifestyle interventions that have been shown to prevent hypertension include maintaining a healthy body weight, taking moderate physical activity, eating a low-sodium diet, reducing alcohol consumption, and adherence to a diet rich in fruit and vegetables [10]. Another emerging potential therapeutic lifestyle strategy to prevent or manage hypertension is increasing dietary protein intake [11, 12]. Both increases in dietary protein intake as a macronutrient [12–16], and as smaller doses as bioactive peptides [17–19], have shown the potential to reduce BP. Indeed, evidence exists that plant-based protein sources may be more effective than animal sources; however, these data stem mainly from observational trials and are inconsistent [11, 20]. Randomized controlled trials comparing plant-based protein sources to animal-based protein sources are limited [12, 21–23]. An essential plant-based protein source that may have anti-hypertensive properties is hemp seed.

Hemp seed (*Cannabis sativa* L.) utilization into foods has been limited due to legislation restricting the cultivation of all *Cannabis* species on account of the presence of varieties high in the psychoactive compound tetrahydrocannabinol (THC). However, as of 1998 in Canada, cultivation of hemp seed containing < 0.3% THC has been allowed. Despite heightened consumer demand for hemp food products, due to historical restrictions on the growing of hemp, the nutritional science literature on hemp-seed protein (HSP) remains limited [24]. HSP has a unique amino-acid profile, with high levels of arginine, which makes HSP an ideal protein to consume for BP-reducing effect, or from which to make BP-reducing bioactive peptides [25].

Both observational and intervention trials have identified associations between dietary protein intake and BP [11, 12, 22]. A meta-analysis of 40 randomized controlled trials demonstrated that replacing a median of 40 g/day of dietary carbohydrate with dietary protein is associated with small reductions in both systolic − 1.76 mmHg (95% confidence interval (CI) − 2.33, − 1.20) and diastolic − 1.15 mmHg (95% CI − 1.59, − 0.71) BP (SBP and DBP, respectively) [22]. The meta-analysis did not find a difference between animal- and plant-based-protein sources in terms of BP-lowering effect. However, trials specifically comparing animal proteins to vegetable proteins are limited and have inconsistent results.

The anti-hypertensive effects of protein may not only be related to the amount of protein in the diet but may also be related to the type of protein. Whether a protein is animal or plant based is likely not as important as the type of amino acids contained in the protein source in terms of BP-lowering ability. Animal sources of protein are considered complete proteins, in that they contain an adequate proportion of all nine essential amino acids necessary for human dietary needs. Most vegetable sources individually are not considered complete because they are limited in one or more of the essential amino acids. This is important because the specific amino-acid content of a protein is likely critical to its anti-hypertensive potential. Additionally, different protein sources may affect BP through alternate mechanisms depending on their amino-acid content. Specific amino acids which have been identified as having potential BP-reducing properties include arginine, cysteine, tryptophan and glutamic acid [26].

Casein is the main protein found in cow’s milk [27], with whey protein making up most of the remaining protein. Pal and Ellis [28] investigated the effects of consuming casein or whey protein, compared to glucose, for 12 weeks in 70 men and women using a randomized, parallel-designed trial. Whey- and casein-protein consumption lowered SBP and DBP compared to baseline after 12 weeks and lowered DBP compared to the glucose control. No difference in BP was seen between the two milk-protein fractions. Soybean protein, which has been well-studied for its potential BP-reducing effects [15, 16, 29], is a representative vegetable protein with a high arginine content. This high arginine content may be responsible for some of soybean protein’s anti-hypertensive properties [26]. Unlike soybean, HSP consumption has not been well-characterized in terms of its effects on BP. HSP has even higher concentrations of arginine than soy, casein or whey protein, which may make it an ideal candidate to evaluate for BP control [30]. Consumer demand for hemp food products is growing and health food retailers are looking to add hemp foods to their product offerings. However, hemp foods, unlike casein, whey and soy, have a very limited database of peer-reviewed publications [31–34] outlining the health benefits of consumption due to restrictions in hemp cultivation, which have only recently been lifted in many countries.

Arginine, conditionally an essential amino acid depending on age and health [35], has been shown to reduce BP when supplemented in the diet [35, 36]. The main source of endogenous nitric oxide (NO) is L-arginine, which is oxidized to NO and citrulline by the action of endothelial NO synthase (eNOS) [37]. However, some proteins with incorporated arginine can undergo methylation and, with subsequent proteolysis, can yield methyl-arginine compounds such as asymmetric dimethylarginine (ADMA). ADMA is an endogenous inhibitor of NO synthase and has been shown to reduce the sensitivity of NO synthase to L-arginine. However, ADMA inhibition of NO synthase may be overcome with increased dietary arginine consumption. Additionally, arginine rapidly undergoes catabolism by arginase, a metalloenzyme, which hydrolyzes L-arginine to L-ornithine and urea [38]. Arginase is, therefore, a key regulator of NO availability, and arginase inhibitors are being investigated for their therapeutic potential in the treatment of endothelial function and hypertension [39, 40]. As with ADMA, additional dietary arginine consumption may be able to overcome arginase activity, which limits arginine availability for eNOS and NO production.

Typical sources of dietary arginine are meat, fish and poultry; however, soy protein isolate and HSP also possess higher levels of this amino acid [30, 41], while milk protein is relatively low in arginine [42]. Food-based arginine is well-tolerated with few side effects, making it a better source of arginine than free L-arginine which has been associated with nausea, gastrointestinal discomfort and diarrhea [37]. HSP, due to its high arginine content, is, therefore, a protein source, which should be investigated for its anti-hypertensive effects.

Girgih et al. [25] compared the effects of HSP isolate on the prevention and treatment of hypertension in spontaneously hypertensive rats (SHRs). The replacement of 1% casein on a dry-weight basis in the rat diet with HSP isolate was able to prevent the increase in SBP seen in young growing SHRs over 8 weeks and decreased SBP in adult SHRs with established hypertension. Decreased plasma renin concentrations and angiotensin-converting enzyme (ACE) activity were observed with the HSP feeding. Additionally, Girgih et al. [25] produced an HSP hydrolysate from the enzymatic hydrolysis of HSP isolate. Protein hydrolysates contain bioactive peptides, which are typically produced by enzymatic hydrolysis of food proteins to release short peptide sequences [43]. However, bioactive peptides can also be produced endogenously through the digestion of dietary proteins [19]. Numerous bioactive peptides have been shown to modulate RAAS via inhibition of ACE and renin activity [44]. The HSP-derived bioactive peptides made by Girgih et al. [25] were able to lower SBP in adult SHRs with established hypertension and decreased SBP in young growing SHRs to a greater extent than the HSP isolate when substituted for casein at 1%. The HSP-derived bioactive peptides also reduced renin concentrations and ACE activity more than did the HSP isolate in the SHRs, and even reduced plasma ACE activity in the normotensive control rats.

Since there was no difference in the degree of reduction in SBP in the adult SHRs between HSP isolate and bioactive peptide, but the reduction in ACE activity was much greater with the bioactive peptide [45], it was hypothesized that the intake of HSP isolate was likely lowering BP via a different mechanism than the peptide [25]. Indeed, the marked difference in the arginine content between the HSP isolate and the hemp seed protein hydrolysate (HPH) could be responsible for the differing hypotensive mechanisms. The HSP isolate contained more than six times the arginine in the HSH-derived bioactive peptides [25]. However, none of the rats were fed a combination of the HSP isolate with additional HSP bioactive peptides to investigate whether the BP-reducing effects would be additive or synergistic.

Bioactive peptides are specific, short amino-acid sequences that remain inactive when bonded to other amino acids within the primary structure of a food protein, but after release via hydrolysis, the free forms of these peptides can affect biological processes. Bioactive peptides have been shown to act as anti-hypertensive agents by inhibiting in vitro and in vivo renin, ACE and angiotensin-II receptor activities in addition to enhancing blood NO levels [44]. Therefore, there is an interest in characterizing these natural anti-hypertensive compounds so that they can serve as alternatives to anti-hypertensive drugs. Bioactive peptides have the advantage of specificity, with limited side effects, potency and low toxicity such that they can be consumed at high doses [44, 46, 47]. Different types of bioactive peptides, derived from numerous sources including dairy, meat, fish, poultry, canola, buckwheat, algae and hemp, have shown hypotensive effects in animal models [43, 44].

However, only a limited number of the bioactive peptides that have been characterized in animals and in vivo have subsequently been tested in human trials [19]. Most human trials investigating dietary bioactive peptides have been derived from dairy products, with the results from casein- and whey-derived bioactive-peptide feeding trials being mixed [19, 48]. A meta-analysis of human trials investigating dairy-derived bioactive peptides found that the consumption of 2–5 g of bioactive peptides a day could yield approximately 5-mmHg and 2-mmHg reductions in SBP and DBP, respectively. It has been suggested that the amino-acid composition of the bioactive peptides may be critical to the ability of the peptide to inhibit ACE activity. Bioactive peptides with a positive charge due to arginine or lysine residues are thought to be being beneficial for ACE inhibition [49]. A 3-week crossover human intervention trial conducted by our team fed 3 g per day of pea-protein hydrolysate and led to a 5–6 mmHg reduction in SBP in the second and third weeks compared to placebo [18]. To our knowledge the addition of bioactive peptides on top of increased dietary protein has not been previously investigated in humans.

While there is good evidence that replacement of dietary carbohydrate with protein has anti- hypertensive effects [11–13, 22], numerous gaps in the research still remain. First, comparisons of plant versus animal sources of dietary protein, or high-arginine versus low-arginine sources of dietary protein are limited [11, 22]. Second, the effects of additional dietary protein, where it does not explicitly replace carbohydrate, is not known [22]. Third, human trials investigating HSP consumption are limited [32]. Fourth, human trials involving non-dairy-derived bioactive peptides are limited [19]. Lastly, no trials investigating the potential benefit of increased dietary protein plus bioactive peptides have been completed to our knowledge. To address these knowledge gaps, we propose a clinical trial that would evaluate the anti-hypertensive potential of consuming whole HSP, and HSP+, compared to casein protein using a randomized, double-blinded and crossover design. This design should be able to address the knowledge gaps identified above. Although little work has been done in humans in this specific area, for the following reasons we were not able to perform a pilot trial before the main study; the long-term nature of this study was the main factor that prevented us considering a pilot study as the first phase. The recruitment of 35 participants and obtaining their consent to enter a long-term trial was a challenge so, recruitment of more people as a pilot group would increase the duration of study. So, we had to recruit more people to start the main study or have the pilot group on an extra washout period to be able to start the trial over. These participants might lose their interest in continuing with the study and the drop-out rate would increase. In terms of testing the procedure, we mainly followed similar clinical trials with other treatments to evaluate the acceptability of the procedure in the following criteria; treatment consumption frequency, treatment consumption under supervision, free-living trial with basic recommendations for physical activity and alcohol consumption, method and frequency of the outcome measurements, method of randomization and follow-up with participants. Acceptability of the treatments were assessed using a taste and texture testing with random participants. Sample size was calculated based on the expected change in the main outcome using similar studies considered 24-h SBP as their main outcome.

## Methods/design

### Objectives and hypothesis

The aim of this study is to assess the hypotensive potential of consuming whole HSP, and HSP+, compared to casein protein in patients with hypertension. The hypotheses to be tested in this study are as follows: Hypothesis 1: consumption of 50 g/day of dietary protein, of any type (casein, HSP or HSP+) for 6 weeks will lead to reduced 24-h SBP compared to baseline. Hypothesis 2: consumption of 50 g/day of hemp-based dietary protein (HSP and HSP+) for 6 weeks will reduce 24-h SBP compared to casein. Hypothesis 3: consumption of 45 g/day hemp protein with an added 5 g/day of HSP+ for 6 weeks will reduce 24-h SBP compared to 50 g/day of HSP.

### Study design

An interventional, randomized, double-blind, crossover, phase-II clinical trial is being conducted at the Clinical Nutrition Research Unit at the Richardson Centre for Functional Foods and Nutraceuticals (RCFFN), University of Manitoba. The trial will consist of three treatment periods of 6 weeks each, separated by 2-week washout periods. A summary of the proposed trial design is presented in Fig. 1. The Standard Protocol Items: Recommendations for Interventional Trials (SPIRIT) Checklist is presented in Fig. 2 and Additional file 1.

**Fig. 1 Fig1:**
[figure not shown]
Schematic flow diagram of the trial protocol

**Fig. 2 Fig2:**
[figure not shown]
Representation of the trial enrollment, interventions and analysis

During each treatment period, participants need to come to the RCFFN twice a week on Tuesdays and Fridays to consume one treatment under supervision and pick up treatments for the next 2 or 3 days. Each treatment consists of a frozen fruit smoothie (mango or pineapple), fruit juice (diet mango juice), sorbet and 25 g of protein from treatment-protein powder and the treatments will be consumed twice a day. HSP and the HSP+ powder has a green color and a stronger taste than casein-protein powder; however, our team has identified that by using a combination of frozen fruit and sorbet in the fruit smoothies this color and taste can be well-masked.

Participants will be instructed to consume two or less alcoholic beverages and no more than three 8-oz. cups of caffeine-containing beverages per day during the trial period. Participants will be instructed to perform their normal daily activities during the measurement day. Prolonged intense physical activity will be discouraged on measurement days and the days preceding measurement days. Participants will be strongly recommended to maintain consistency in their physical activities and dietary pattern during the trial period. A 3-day food record will be collected during the first day of the first phase and during the final week of each treatment period to be analyzed for calorie intake during the study.

During the study period, body weight will be monitored as a change could occur due to the inclusion of extra protein in a free-living condition. All outcome variables will be adjusted for changes in body weight should significant changes occur between treatments. Gastrointestinal tolerability and weekly monitoring questionnaires will be completed by participants weekly during each intervention period.

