### Statistical analysis

Statistical analysis will be performed in an intent-to-treat fashion. In addition, a per-protocol analysis will also be performed to check for potential effect attenuation due to unequal compliance or protocol deviations across treatments. Statistical analysis will be performed using SAS 9.4. The endpoint of treatments and baselines will be compared using a mixed-model analysis of variance. Sequence and sex will be included as fixed factors, and participant will be included as a random factor, with participant repeated by period.

Dunnett’s test will be used to adjust for multiple comparisons with the endpoint of the baselines set as the control. Effects of treatment by time on measures repeated during treatments will be assessed using a mixed-model analysis of variance with sequence, sex, time as fixed factors and participants included as random factors, with participants repeated by period, with Tukey-Kramer adjustments for multiple comparisons. Model residuals will be visually inspected to assess independence, normal distribution, and constant variance. Datasets with residuals determined to violate these assumptions will be transformed prior to re-analysis. Results will be expressed as estimated least square means ± standard error of the mean (SEM) for all values. Statistical significance will be set at *p* < 0.05 for all analyses.

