## Discussion

Unlike earlier trials which have compared carbohydrate to protein in terms of BP, the currently proposed trial will compare different types of protein added into the participants’ diet. In this instance, the participant may or may not replace existing calories in the diet with the additional protein. Therefore, the potential exists that increased protein consumption will lead to a change in overall energy intake. An increase in energy intake could occur if the additional calories of the protein are not being compensated for by participants, or a decrease in energy intake could occur due to the satiating properties of protein compared to other macronutrients. These potential shifts in overall energy intake could result in changes in body weight, which could lead to BP changes. Therefore, outcome variables, such as BP, will be adjusted for any significant changes in body weight, which may occur during the treatment periods. Additionally, the mix of fat and carbohydrate being potentially replaced by protein in terms of energy intake may vary between participants. While this trial will not be able to determine exactly whether fat or carbohydrate energy is being replaced with protein, it will reflect the real-world impact of instructing patients and the general public to increase protein consumption by drinking protein smoothies, without specific counseling on replacing other foods.

As in all clinical trials with food-based treatments, potential differences in taste, texture and smell can make the blinding of participants to the treatments difficult. Our research team has worked with HSP and has developed a smoothie recipe which is good at masking the type of protein powder from which it is made. However, if this blinding is not sufficient it may be possible for participants to identify the casein treatment versus the HSP and HSP+ treatments. The likelihood of participants being able to identify the HSP compared to the HSP+ treatment is low. Fortunately given the crossover design and the stringent monitoring of compliance in the proposed trial, it is unlikely that any un-blinding of the participants to the treatments, as described above, would be able to impact the results. All of the outcomes in this trial will be objectively measured; therefore, the impact of knowing if you are on a hemp-based treatment is unlikely to change your outcome measurements.

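### Outcomes, including 24-h SBP, are to be adjusted for on-treatment weight change only if that change is significant, so a pre-test decides which effect is reported

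*Protocol article*

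**What the plan says.** Methods/design, Study design, explains why weight is followed: "body weight will be monitored as a change could occur due to the inclusion of extra protein in a free-living condition". It then sets the rule: "All outcome variables will be adjusted for changes in body weight should significant changes occur between treatments".

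The Discussion gives the reasoning. Participants may eat more in total, or less because protein is satiating, and "These potential shifts in overall energy intake could result in changes in body weight, which could lead to BP changes". It restates the rule as "outcome variables, such as BP, will be adjusted for any significant changes in body weight, which may occur during the treatment periods". The same paragraph says of the trial that "it will reflect the real-world impact of instructing patients and the general public to increase protein consumption by drinking protein smoothies", without counselling on replacing other foods.

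The Statistical analysis section describes a model without weight: "Sequence and sex will be included as fixed factors, and participant will be included as a random factor, with participant repeated by period". It does not mention the conditional rule, and nowhere does the protocol say that the unadjusted result stays primary.

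**The concern.** There are three problems.

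1. **The covariate is a consequence of treatment.** By the protocol's own account, protein changes energy intake, energy intake changes weight, and weight changes blood pressure. Conditioning on weight change removes that route and no longer estimates the total effect of the assigned treatment. The hemp–casein and HSP+–HSP comparisons also lose the protection of randomisation, because diet, activity or sodium intake may drive both weight and blood pressure.
2. **A test on the trial's own data picks the estimand.** The adjustment enters only if weight change is significant, which is most likely when weight carries part of the effect. The final p-value and confidence interval take no account of that step.
3. **The two triggers differ.** Study design requires a difference between treatments. The Discussion requires only a significant change during the treatment periods. If weight moved equally on all three proteins, the second trigger would be met and the first would not. The analyst could then choose after seeing the data, and Hypothesis 1 (any protein versus baseline) would be directly affected.

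The primary estimate, its p-value and its meaning are all at stake.

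**Working it through.** **The plan's own figure.** Sample size section: change of 4 mmHg, within-participant SD 5.45 mmHg, power 0.80, α = 0.05 (taken as two-sided).

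N = 2 × 5.45² × (1.960 + 0.842)² / 4² = 29.14, rounded up to 30. The stated 30 reproduces. Power for one paired contrast at N = 30 is 0.81 by the normal formula and 0.78 with a t distribution on 29 degrees of freedom, so there is little to spare.

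**Assumed inputs (not in the protocol).**
- Weight difference between hemp and casein: 0 to 1.0 kg in either direction.
- Slope: 0.5 to 1.5 mmHg per kg.
- Within-participant weight SD: 1 kg, so the SD of a paired weight difference is √2 = 1.41 kg.
- The SD of the paired SBP difference is held at 5.45 × √2 = 7.71 mmHg, and nothing unmeasured affects both weight and SBP.

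**By formula.**
- Adjusted reduction = total reduction − slope × weight difference. Mild end: 4 − 0.5 × 0.5 = 3.75 mmHg. Strong end: 4 − 1.5 × 1.0 = 2.5 mmHg.
- How often the rule fires depends on weight difference ÷ (1.41/√30) = weight difference ÷ 0.258. That is 1.94 at 0.5 kg and 3.87 at 1.0 kg, so it fires in about 46% and 96% of trials.
- Precision also falls. The variance factor goes from 1/N to 1/N + w̄²/Sxx, where w̄ is the mean weight difference and Sxx its sum of squares. At w̄ = 1 kg, Sxx ≈ 29 × 2 = 58, and the factor goes from 0.0333 to 0.0333 + 0.0172 = 0.0506. The standard error rises by √(0.0506/0.0333) = 1.23, before any gain from a smaller residual variance.

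**By simulation.** One paired contrast, N = 30, 20,000 trials per setting, true total reduction 4 mmHg; adjusted when the paired t-test on weight has p < 0.05. Ranges run over slopes 0.5 to 1.5.

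| Weight on hemp vs casein | Rule fires | Reduction when it fires | Reduction when it does not | Mean over all trials | Power under the rule |
|---|---|---|---|---|---|
| Equal | 5% | 4.0 | 4.0 | 4.0 | 0.78 |
| 0.2 kg lower | 11–12% | 3.9–3.7 | 4.0–3.9 | 4.0–3.9 | 0.77–0.76 |
| 0.5 kg lower | 46–47% | 3.75–3.25 | 3.9–3.7 | 3.8–3.5 | 0.70–0.63 |
| 1.0 kg lower | 96% | 3.5–2.5 | 3.7–3.2 | 3.5–2.5 | 0.50–0.30 |
| 1.0 kg higher | 96% | 4.5–5.5 | 4.2–4.9 | 4.5–5.5 | 0.70–0.87 |

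Without the rule, power is 0.78–0.79 throughout. The fourth column shows that the pre-test distorts the unadjusted estimate too: trials in which it is kept have been selected for a small observed weight difference.

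**Sensitivity.** With the SD of the paired weight difference at 1.5–2.0 kg, the rule fires in 26–43% of trials at 0.5 kg and 75–94% at 1.0 kg. At 1.0 kg and 1 mmHg per kg, power is 0.42–0.51.

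**The case against.** The best counter-argument is that the harm needs a weight difference the protocol does not predict. All three arms give the same protein dose in similar smoothies, so satiety and added energy are largely shared. At 0–0.2 kg the bias is at most about 0.1 mmHg and power falls by no more than about 3 points. This stands as a limit on size for the between-protein comparisons. It does not help Hypothesis 1, where a shared weight change is exactly the route described and the Discussion's trigger would apply.

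A weight-independent effect is also a fair question, since the anticipated results rest on arginine, nitric oxide and ACE inhibition. The formal aim does not say whether the weight route counts, and the real-world statement sits in the Discussion. This stands too, but it supports a separate mechanistic analysis and not a switch made by a p-value.

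The statistical section has no weight term, so the unadjusted result might be reported anyway. The protocol does not say so, while the rule as written covers all outcomes. A separate analysis plan could add detail but would have to overrule a rule the protocol already fixes.

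Finally, adjustment does not always shrink the effect: if weight is higher on the better treatment, it inflates it. That is correct, and in both directions the total effect is no longer estimated.

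**Conclusion.** The concern holds. As written, a significance test on a variable caused by treatment decides whether 24-h SBP is reported as a total or a weight-adjusted effect, and the two statements of the rule disagree on the trigger. The weight-adjusted figure also sits badly with the real-world reading the Discussion gives the trial.

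The size depends on assumed weight inputs. At 0.5–1.0 kg lower weight on hemp, the reported reduction averages 3.8 to 2.5 mmHg instead of 4, with power of 0.70 to 0.30. At 1.0 kg higher it averages 4.5 to 5.5 mmHg. With no true weight difference there is no bias. If other factors drive both weight and blood pressure, the adjusted figure is not a clean direct effect either.

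**What to change.** - State in the Statistical analysis section that the primary and secondary analyses are not adjusted for weight change after randomisation, whatever the weight data show.
- Report weight change by treatment as an outcome in its own right.
- Keep the weight-adjusted analysis as a pre-specified supportive analysis, always run, labelled mechanistic, with the assumption of no unmeasured common causes of weight and blood pressure stated.
- Delete the conditional sentence in Study design and its variant in the Discussion.

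Weight is already measured on days 1 and 41 of each period, so no new data are needed and the sample size does not change. The cost is an amendment through the approvals listed under Protocol modification (principal investigator, ethics board, Health Canada directorate) and a registry update. It should be in place before blood pressure or weight is analysed by treatment label.
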